#### Safety endpoints

Incidence and severity of adverse eventsIncidence of side effects due to medication commenced during the trial, for the modulation of any PAD risk factor. This includes any drug interaction of these medications with any previously assumed medication the patient was using regularly prior to commencing the trial.

### Sample size calculation

For sample size calculation, the EUROACTION study [30] was used to estimate the coefficient of variation for sample proportions.

Data from the EUROACTION [30] study suggest that 12-week intervention response rates for the primary endpoint of 54.8% (intervention programme) and 35.6% (usual care). Eighty percent statistical power and an alpha level of 5% were chosen. A two-sample comparison of proportions sample size calculation was implemented.

With these parameters, the G*Power [31] software yields a trial with a maximum sample size of 208 patients completing the intervention (104 per intervention group).

### Statistical analysis

All data will be analysed according to the intention to treat principle. The primary outcome, the achievement of treatment goals for PAD risk factors between both groups at 12 weeks and 12 months will be compared using chi-square or Fisher’s exact where appropriate. Secondary outcomes including time to event will be assessed using Kaplan-Meier survival curves and log rank test. An exact 95% confidence interval will be applied for the difference between intervention groups in terms of PAD risk factor reduction.

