## Methods

### Study design

This is a randomised, parallel group, active-control trial to compare the effectiveness of the risk factor modification intervention programme to standard healthcare in a tertiary vascular care centre, in the reduction of the prevalence of modifiable risk factors in PAD patients.

This trial will randomise patients with PAD in an equal ratio to one of two treatment arms. One arm will be randomised to undergo a risk factor modification intervention programme at a community-based centre. The other arm will be provided with standard healthcare advice, in the outpatient PAD clinic in a tertiary referral vascular centre. Patients randomised into the risk factor modification intervention programme will have the intervention administered for 12 weeks. Patients will then be followed for 12 months to determine further PAD outcomes. The participant flowchart through the study is shown in Fig. 1. SPIRIT figure for this trial is given in Fig. 2.

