### Randomisation

After meeting the inclusion criteria, screened patients will be randomised to one of two treatment arms. One arm will receive the 12-week intensive risk factor modification intervention programme. The control arm will be provided with standard care in the outpatient PAD clinic. This is an intention to treat designed study, where patients are analysed as randomised. Each screened patient will be given a unique screening number.

Screened patients will be randomised in a 1:1 ratio of study intervention: control according to a randomisation scheme. The randomisation scheme will be produced using the PROC PLAN® procedure of the SAS®software package (version 9.2.2) using a simple randomisation strategy. The scheme will be concealed from all patients and study personnel until after database lock.

Patients will be allocated to intervention via an automated telephone system, which will not deliver the randomised allocation except after registering the subject screening number. Each screened patient who is recruited to the trial will be given a unique patient trial number.

The statistician will remain blinded to the treatment allocation until all the data have been analysed to minimise bias. Outcome assessors and data analysts will be blinded; however, in the event of an adverse event outcome, assessors will be unblinded.

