### Intervention

#### Risk factor modification structured Programme

The risk factor modification intervention programme is a 12-week intensive lifestyle programme. This is a nurse-led, community-based, lifestyle and risk factor modification intervention modelled on the European Society of Cardiology demonstration project, a large clinical trial called EuroAction [30]. The programme includes:
Phase 1: Initial individualised assessment by the multidisciplinary team (MDT) will include previously mentioned baseline assessment in addition to the following:
Dietician will assess, current eating habits and food diaryExercise specialist will assess 7-day activity recall, barriers to exercise, 7-day pedometer and Functional Capacity TestPhase 2: The intervention including:
Weekly exercise class and educational workshops.Serial blood pressure, body mass index, waist circumference, glucose and lipid measurements with goal setting.Weekly MDT meetings.Targeted and protocol-based pharmacotherapy to support lifestyle changes.

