#### Standard healthcare

The control group will receive the standard healthcare advice provided to PAD patients in the outpatient PAD clinic. In this study, standard care will be conducted by the researchers which include:
Advising patients to quit smoking, regular exercise and healthy eating, but neither structured intervention nor organised cessation plans will be addressed.Non-specific interventions, such as providing patients with educational material on general health problems.

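### The programme arm is treated in classes, but the sample size, primary test and interval assume independent patients; the stated 80% power therefore rests on no correlation between classmates

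*Protocol article*

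**What the plan says.** Allocation is by patient: "Screened patients will be randomised in a 1:1 ratio of study intervention: control according to a randomisation scheme" (Randomisation). The Intervention section describes a 12-week nurse-led programme whose second phase includes "Weekly exercise class and educational workshops", together with individual assessment, serial measurements with goal setting, and drug treatment by protocol. Study setting places all of it in one community centre. Controls are advised in the hospital clinic, where "neither structured intervention nor organised cessation plans will be addressed" (Standard healthcare).

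For the sample size, "A two-sample comparison of proportions sample size calculation was implemented". The inputs are 54.8% against 35.6%, 80% power and 5% alpha, and the result is 208 completing patients, 104 per group. The primary outcome "at 12 weeks and 12 months will be compared using chi-square or Fisher’s exact where appropriate", with an exact 95% confidence interval for the difference between groups. No class size, ICC or design effect appears.

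**The concern.** Individual randomisation makes patients independent at entry, but not necessarily at outcome. Programme patients who attend the same classes share peers and whatever varies in delivery from one class to the next. Their chances of stopping smoking or reaching a BMI, HbA1c or cholesterol target may then move together. Controls share no classes. The design is therefore partially nested: possibly clustered in one arm, independent in the other.

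A positive correlation inflates the variance of the programme-arm proportion only. An analysis that ignores it gives a standard error that is too small, and a power calculation that ignores it is optimistic. This is not a detail left to an analysis plan, because the protocol itself fixes the test, the interval and the sample size on the independence assumption.

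**Working it through.** **Inputs from the protocol.** p1 = 0.548, p2 = 0.356, difference 0.192, n = 104 per arm, alpha 5% (taken as two-sided, which reproduces the stated size; one-sided would need only 83 per arm).

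**Assumed, because the protocol does not give them.** Class size m of 5 to 15; ICC of 0.01 or 0.05. A size near 8 is a plausible midpoint: recruitment from 1 June 2018 to 1 June 2021 is about 156 weeks, or 13 blocks of 12 weeks, and 104/13 = 8. That is the average number in the programme at one time. It is a class size only if each block starts together.

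**1. Reproduce the plan's figure.** The two-sided calculation gives 105 per arm with pooled variance, 102 unpooled and 104.1 by the arcsine method. Power at 104 per arm is 79.9% pooled. The stated 208 is thus the plain independent-patient answer and holds no allowance for clustering.

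**2. Unclustered baseline for the comparison (unpooled).** SE = sqrt(0.548×0.452/104 + 0.356×0.644/104) = sqrt(0.002382 + 0.002204) = 0.0677. Power = Φ(0.192/0.0677 − 1.96) = Φ(0.875) = 80.9%. The clustered figures below use the same unpooled formula, so 80.9%, not 79.9%, is their proper comparator.

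**3. Add clustering in the programme arm only.** D = 1 + (m − 1)×ICC, and SE = sqrt(D×p1(1−p1)/104 + p2(1−p2)/104). For m = 8 and ICC 0.05: D = 1.35, SE = 0.0736, power = Φ(2.608 − 1.96) = 74.2%.

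**4. Type I error of the plain chi-square.** 2×(1 − Φ(1.96/sqrt((D + 1)/2))). This applies where class effects exist but average to zero.

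| ICC | m | D | SE ratio | Power | Plain chi-square type I error |
|---|---|---|---|---|---|
| 0 | any | 1.00 | 1.00 | 80.9% | 5.0% |
| 0.01 | 5 | 1.04 | 1.01 | 80.1% | 5.2% |
| 0.01 | 8 | 1.07 | 1.02 | 79.5% | 5.4% |
| 0.01 | 15 | 1.14 | 1.04 | 78.2% | 5.8% |
| 0.05 | 5 | 1.20 | 1.05 | 77.0% | 6.2% |
| 0.05 | 8 | 1.35 | 1.09 | 74.2% | 7.1% |
| 0.05 | 12 | 1.55 | 1.13 | 70.6% | 8.3% |
| 0.05 | 15 | 1.70 | 1.17 | 68.0% | 9.2% |

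**5. Checks.** With pooled variance throughout, m = 8 and ICC 0.05 gives 73.1% against 79.9%, a similar loss. Beta-binomial simulation at m = 8, ICC 0.05 and a 35.6% response in both arms puts plain chi-square at about 7%. A Fisher-type test comes out at about 5%, from 3.6% without clustering.

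**The case against.** The strongest reply is that the protocol defines no clusters. It states neither class size nor whether entry is closed or rolling, and recruitment runs continuously for three years. With rolling entry, class membership overlaps and a start cohort only approximates it. This stands, and it is why no single figure can be given.

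Second, the shared team is not itself a source of clustering. If one team runs every class, its influence is common to the whole arm and belongs to the treatment effect. Only what differs between classes counts: peers, and drift in delivery over time. That also stands.

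Third, the ICC may be small. The endpoint is met by any one of four individual criteria, two of which, HbA1c and cholesterol, also respond to individually prescribed drugs. The classes end at 12 weeks, so correlation may have faded by one year. At ICC 0.01 the loss is at most about 3 points of power.

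Fourth, a reader might infer that the trial's false-positive rate is 7% or more. The documents do not support that. If the programme changes nobody's outcome, individually randomised patients remain independent and the test keeps its size. The excess needs real class effects that cancel on average. It also belongs to plain chi-square: Fisher's exact test, which the protocol allows, is conservative and absorbs much of it at modest ICC. That conservatism has a price, since Fisher's power at 104 per arm is 75.1% even with no clustering.

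None of this removes the mismatch between how one arm is treated and what the named methods assume.

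**Conclusion.** The point holds in conditional form. The protocol's sample size, test and interval assume independent patients, whereas one arm attends classes. If classmates' outcomes correlate, the programme-arm variance is understated. The stated 80% is then the power at ICC 0, with no more than about one point to spare on the more favourable formula.

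Assuming 5 to 15 per class, power is 78-80% at ICC 0.01 and 68-77% at ICC 0.05, against 80.9% like for like. The standard error should be 1-4% or 5-17% larger. Plain chi-square type I error is about 5.2-5.8% or 6.2-9.2% where class effects exist but average to zero, and lower with Fisher's exact test. Class size and ICC are assumptions throughout, and near ICC 0.01 the effect is minor.

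A reader might go further and say that the trial's true power is 74%. The documents do not support this: that figure is one cell of the table and needs two inputs the protocol does not contain.

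**What to change.** - Record the class start cohort of every programme patient.
- Pre-specify the primary risk difference with a partially nested variance: class cohorts as clusters in the programme arm, each control as a cluster of one, with a small-sample correction. Report it beside chi-square or Fisher's exact test at both time points.
- Report the estimated ICC with the results.
- In Sample size calculation, state that 80% power assumes independent outcomes within classes, and give the range above as labelled assumptions rather than one replacement figure.

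The cost is one data field, some analysis wording, a slightly wider interval and a less favourable power statement. With about 13 cohorts the ICC will be estimated imprecisely and the small-sample correction will matter. If entry is rolling, the clusters are only approximate, which the report should say. No extra patients are needed.

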### Eligibility criteria

#### Inclusion criteria

Aged 18 years or moreProvide written informed consentPAD: diagnosed by at least one of the following:
Ankle-brachial index of less than 0.90 in at least one lower extremity [9]Toe brachial index of less than 0.60 [9]Evidence of arterial occlusive disease in one lower extremity detected by duplex ultrasonography, computed tomographic angiography, or magnetic resonance angiography [9]Symptomatic PAD (Rutherford category 2 and above [19])Patients should have at least one of the following risk factors:
Blood pressure > 140/80 mmHgFasting blood sugar (FBS) > 53 mmol/molGlycosylated haemoglobin (HbA1c) > 7%Total cholesterol > 5 mmol/LLow-density lipoprotein (LDL) cholesterol > 2.6 mmol/LTriglycerides > 1.7 mmol/LHigh-density lipoprotein (HDL) < 1.0 mmol/L in men and < 1.2 mmol/L in womenPhysical activity less 30 min for 5 days per weekBody mass index (BMI) > 25 kg/m^2^Waist circumference > 80 cm in women, and > 94 cm in menCurrent smoker or exposure to tobacco in any formUnhealthy diet, Mediterranean diet score less than 10 points

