### Study screening

Patients with Symptomatic PAD (Rutherford category 2 and above [19]) will be invited to join the study. Invited patients will be provided with a pre-designed information leaflet. This leaflet will be fully explained to the patient at the initial assessment. The study researchers will answer any questions about the study. Informed consent will be obtained from the patient on a formatted consent form. Patients will be given the freedom to give consent either on the same day or at a later date in accordance with a study within a trial (SWAT), entitled “Same-day Consent vs Delayed Consent in a Randomised Trial: A Study within a Trial” [21]. This SWAT aims to ensure the rigorousness of the consent process and will run in conjunction with this randomised controlled trial.

Researchers will screen the patient for inclusion and exclusion criteria and administer a series of the following:
Record PAD risk factors such as smoking, hyperlipidaemia, diabetes, hypertension, increased body weight and the patient’s current medication.Document the Rutherford category [19], claudication distance and absolute walking distance for each patient, to assess the severity of PAD.Schedule appointments for baseline health assessments over the following month.

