#### Secondary endpoints

Secondary endpoints of PAD outcomes are based on the Society for Vascular Surgery (SVS) reporting standards [17]:
Amputation-free survival; defined as time spent free from any major above ankle amputation [17]Hemodynamic improvement: defined as an increase in the ABI by at least 0.10 [17]Clinical improvement: which is defined as an upward shift by at least one Rutherford category. However, PAD patients suffering from actual tissue loss (Rutherford category 5 [19]) should move up two Rutherford categories to be considered improved [19].Re-intervention or stenosis rate; any re-intervention or stenosis among patients who already underwent vascular surgery [17]Freedom from major adverse cardiovascular events (MACE). MACE is defined as any major cardiovascular event such as myocardial infarction, cerebrovascular accident or death [17].Major adverse limb events (MALE). MALE is defined as any major amputation or revascularization procedure [17].Revascularisation-free survival; defined as time free from any revascularisation procedure regardless of if it were an endovascular intervention or an open surgery [17].Change from baseline of the following risk factors:
a-BMI (measured in kg/m^2^)b-HbA1c (measured as a percentage)c-Total cholesterol (measured in mmol/L)Health-related quality of life [18]; assessed using the Dartmouth Cooperative Information Project (COOP) charts at enrolment and after 1 year. The COOP charts measure six core aspects of functional status: physical fitness, feelings, daily activities, social activities, change in health, pain, and overall health. The instrument consists of six charts, referring to the abovementioned aspects of functioning. Each chart consists of a simple title, a question referring to the status of the patient and an ordinal 5-point response scale illustrated with a simple drawing. Each item is rated on this 5-point ordinal scale ranging from 1 (no limitation at all) to 5 (severely limited); for “change in health” score 1 means “much better” and score 5 “much worse”. The designers do not advocate summing the responses to gain a single index figure of health status

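### The log-rank test for the limb time-to-event endpoints names no stratum, although Rutherford category is recorded before allocation: a small, avoidable loss of power and no correction for a chance imbalance in severity

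*Protocol article*

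**What the plan says.** The Statistical analysis section of the protocol article covers the time-to-event endpoints in one sentence: "Secondary outcomes including time to event will be assessed using Kaplan-Meier survival curves and log rank test". It names no stratum, covariate or hazard ratio.

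Four other places bear on that choice.

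- **Entry (Study screening; the same threshold is in the Inclusion criteria).** "Patients with Symptomatic PAD (Rutherford category 2 and above [19]) will be invited to join the study". No upper category is set.
- **Tissue loss is expected (Secondary endpoints).** The definition of clinical improvement has its own rule for such patients: "PAD patients suffering from actual tissue loss (Rutherford category 5 [19]) should move up two Rutherford categories to be considered improved".
- **Severity is known before allocation (Study screening).** Researchers are to "Document the Rutherford category [19], claudication distance and absolute walking distance for each patient, to assess the severity of PAD".
- **Allocation (Randomisation).** The scheme is 1:1, produced "using a simple randomisation strategy", so it does not balance severity.

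The endpoints most clearly concerned are amputation-free survival ("Amputation-free survival; defined as time spent free from any major above ankle amputation") and revascularisation-free survival, which is also defined as a time free from an event.

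**The concern.** The limb endpoints pool patients with claudication and patients with tissue loss, whose one-year risk of amputation or revascularisation can be expected to differ. A log-rank test that ignores a strong prognostic factor loses some power. It also has no way of correcting for one arm receiving more of the severe patients by chance. Simple randomisation permits such an imbalance, and the variable needed to handle it is already collected before allocation.

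These endpoints carry the clinical part of the hypothesis. The Background expects better clinical outcomes and fewer amputations, and the Secondary objectives include amputation-free survival and the need for revascularisation. The trial is sized only for risk-factor goals, and follow-up is 12 months, so limb events may be few and the information in them should not be wasted.

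**Working it through.** **1. The plan's own figure.** The Sample size calculation gives 208 patients (104 per group) for 54.8% versus 35.6%, with 80% power and 5% alpha. A two-sided comparison of two proportions gives 105 per arm (pooled variance) or 104.1 (arcsine), and power at 104 per arm is 79.9%. The figure reproduces. It concerns the primary endpoint only; no event count or power is stated for the time-to-event endpoints.

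**2. How often simple randomisation leaves severity unbalanced.** Call category 4 and above severe, with share p (assumed). With N = 208 allocated 1:1, the SD of the between-arm difference in that share is sqrt(4p(1 − p)/N), and the chance of a gap above 10 percentage points is 2(1 − Φ(0.10/SD)).

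- p = 0.15: SD = sqrt(4 × 0.1275/208) = 0.050; chance 4%
- p = 0.30: SD = sqrt(4 × 0.21/208) = 0.064; chance 12%
- p = 0.50: SD = sqrt(4 × 0.25/208) = 0.069; chance 15%

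**3. Power, plain versus stratified.** Simulation with N = 208, simple 1:1 allocation, exponential event times censored at one year, two severity groups and a two-sided 5% test. Severe shares, one-year control risks and hazard ratios (HR) are all assumptions. The first five rows used 4,000 trials each, the last four 6,000.

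| Severe share | Risk, less severe / severe | HR | Plain | Stratified | Gain (points) |
|---|---|---|---|---|---|
| 30% | 10% / 40% | 0.5 | 42.9% | 45.9% | 3.0 |
| 30% | 10% / 60% | 0.5 | 47.2% | 58.1% | 10.9 |
| 50% | 10% / 50% | 0.5 | 58.8% | 66.0% | 7.2 |
| 15% | 10% / 50% | 0.5 | 36.6% | 41.4% | 4.8 |
| 30% | 3% / 25% | 0.5 | 23.2% | 24.7% | 1.5 |
| 30% | 10% / 40% | 0.7 | 15.8% | 17.6% | 1.8 |
| 30% | 10% / 40% | 0.8 | 9.6% | 9.8% | 0.2 |
| 30% | 3% / 25% | 0.7 | 10.6% | 11.7% | 1.1 |
| 15% | 2% / 15% | 0.5 | 11.7% | 11.9% | 0.2 |

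The gain is large only when the risk gradient is steep and the effect strong. It nearly vanishes with a weaker effect or few events.

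**4. Rejection rate with no treatment effect.** Settings as in the first five rows above, with HR = 1. The last two columns use only the trials in which the severe share differs by 10 points or more.

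| Severe share | Risks | Plain, all trials | Stratified, all trials | Plain, imbalanced | Stratified, imbalanced |
|---|---|---|---|---|---|
| 30% | 10% / 40% | 4.9% | 4.5% | 10.3% | 4.8% |
| 30% | 10% / 60% | 5.2% | 5.5% | 14.1% | 4.7% |
| 50% | 10% / 50% | 4.6% | 5.0% | 10.4% | 6.0% |
| 15% | 10% / 50% | 5.4% | 5.4% | 15.0% | 3.6% |
| 30% | 3% / 25% | 4.9% | 4.7% | 10.0% | 5.3% |

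Over all randomisations both tests hold the 5% level. Given a marked imbalance, the plain test rejects about 10 to 15% of the time and the stratified test about 4 to 6%. The conditional figures are less precise. In the first row about 0.109 × 4,000 = 436 trials qualify, so the standard error is about sqrt(0.103 × 0.897/436) = 1.5 points. In the fourth row about 0.042 × 4,000 = 168 qualify, giving sqrt(0.15 × 0.85/168) = 2.8 points.

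**The case against.** **The SAP may already stratify.** This is a condensed article, its abbreviation list includes a SAP, and the sentence does not say that the test is unstratified. Silence on strata alone would not be a finding. The point stands because the article does fix a test, and a log-rank test with no stratum named is ordinarily read as the plain one. If the SAP stratifies, the two documents only need to be aligned.

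**The test is valid.** This is correct. A reader might infer from the 10 to 15% figure that the type I error is inflated or the comparison biased. The second table shows otherwise: that rate applies only given a marked imbalance, and trials with smaller imbalances offset it. Where the gradient is weak or events are few, a further run found even the conditional rate at 3 to 6%.

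**The gain may be negligible.** This stands in part. An HR of 0.5 for limb events after a 12-week lifestyle programme is optimistic. The Exclusion criteria (immobility, comorbidity limiting participation) may also keep the severe share low. At weaker effects or with few events the gain is about 0 to 2 points, and power is low with either test.

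**The point does not reach every endpoint.** This is also correct. A reader might infer that Rutherford category is the strongest predictor of all the time-to-event outcomes. Nothing in the documents shows that it predicts MACE; with assumed risks of 5% and 8% and HR 0.7, stratifying changes power from 8.9% to 9.0%. MALE is listed without a time-to-event definition, so it is not clearly covered by the log-rank sentence. For limb events, its prognostic value is an assumption consistent with the protocol's use of the category as a measure of severity.

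**Conclusion.** The point holds as a minor one about efficiency and conditional performance, for amputation-free and revascularisation-free survival. The plan compares these by a log-rank test with no stratum, while a pre-allocation severity measure is available and allocation does not balance it. The documents support neither a claim of bias nor one of overall error inflation, and the primary result is not affected.

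Assuming 15 to 50% severe patients and hazard ratios of 0.5 to 0.8, stratifying is worth between almost nothing and about 11 points of power. Its firmer benefit is protection in the minority of trials where severity happens to be unbalanced, provided the risk gradient is steep enough. Every size given rests on assumed event rates, severity mix and treatment effect, because the documents give none.

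**What to change.** In the Statistical analysis section, or in the SAP before unblinding, state that amputation-free and revascularisation-free survival will be compared by a log-rank test stratified by the Rutherford category recorded at screening (for example 2–3 versus 4 and above). Add a hazard ratio with 95% CI from a Cox model stratified the same way. Keep the Kaplan-Meier curves and report the plain log-rank test as supportive. For freedom from MACE, stratification is optional.

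Use the screening value. The Baseline section describes assessments in patients already randomised, so only the screening value is clearly recorded before allocation. Fixing the stratum now is also better than adjusting after an imbalance has been seen, which is open to challenge. The Randomisation section keeps the statistician blinded until the data have been analysed, so the choice can still be made without knowledge of results.

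The cost is a sentence or two of analysis wording, with no new data, visits or patients. The cut-point is a judgement and should be fixed in advance. The Cox hazard ratio will describe the effect within severity groups, which should be stated. If severe patients or events are few, little is gained.
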